### Aims

In this pilot study, the primary aim will be to investigate take-up, drop-out and completion rates of the online course and the completion rates for data collection.

Secondary outcomes will be mood ratings at 3 months. We will use changes in the Patient Health Questionnaire 9 [13] score to provide data relating to the effect of the intervention on depression levels. This will give an indication of efficacy, together with the drop-out and retention rates.

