## Methods

### Overview

The study will be a parallel, two-arm pilot RCT with a 50:50 allocation ratio across the two groups. Participants will be remotely randomized to receive the online intervention immediately (immediate-access group) or after a 3 month delay following randomization (delayed-access group). The delayed-access group will serve as the control at the primary outcome point. Ethical approval has been granted by the College of Medical, Veterinary and Life Sciences Ethics Committee for Non-Clinical Research Involving Human Subjects, University of Glasgow (Ref. 200140159).

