#### Inclusion criteria

Aged 18 or over.Living in the UK.Ability to understand written and spoken English language.Regular access to a computer, smart phone or tablet with audio and broadband connection.Score of 10 or more on the Patient Health Questionnaire 9.

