### Statistical analysis

Recruitment, uptake and adherence to intervention will be summarized and presented as percentages. Baseline characteristics will be summarized for all participants as well as for the immediate-access and delayed-access groups separately. Two-sample *t* tests or Mann–Whitney tests, depending on distributions, and Fisher’s exact tests will be used to compare the two treatment groups and confirm that participants had been effectively randomized.

To assess efficacy, appropriate linear models will be used, using an intention-to-treat approach. Models will be adjusted for age, sex and antidepressant use at baseline. These models will be used to estimate and test the statistical significance of the within-group change between baseline and 3 months, and the between-group differences at each time point. Rates and characteristics of drop-out will be explored. Progression criteria to a full RCT would be based on adequate recruitment, evidence of possible clinical efficacy and ability to deliver the intervention and collect research data.

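### The efficacy analysis includes significance tests of within-group PHQ-9 change in participants selected for high PHQ-9, and the plan does not say that only the between-group difference counts towards progression

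*Protocol article*

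**What the plan says.** The efficacy paragraph of the Statistical analysis section opens: "To assess efficacy, appropriate linear models will be used, using an intention-to-treat approach". It then gives the models two tasks. The first is within-group: "These models will be used to estimate and test the statistical significance of the within-group change between baseline and 3 months". The second follows in the same sentence: "and the between-group differences at each time point". Neither is marked as descriptive or as the one that decides. The paragraph ends by making evidence of possible clinical efficacy one of the progression criteria, next to adequate recruitment and the ability to deliver the intervention and collect data.

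Three other places bear on this:

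- Inclusion criteria: "Score of 10 or more on the Patient Health Questionnaire 9".
- Aims: "We will use changes in the Patient Health Questionnaire 9 [13] score to provide data relating to the effect of the intervention on depression levels", and then "This will give an indication of efficacy, together with the drop-out and retention rates".
- Overview: "The delayed-access group will serve as the control at the primary outcome point".

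Regression to the mean and natural recovery are not mentioned.

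**The concern.** Participants enter because they score high on one questionnaire, and change on that questionnaire is then the measure of effect. Unless baseline and 3-month scores are perfectly correlated, the mean of such a group is expected to fall at the second measurement with no treatment at all. People who answer an advertisement while feeling low also tend to recover somewhat over three months. Both forces act equally on the two arms. The randomised comparison removes them; a test of change within one arm does not.

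At stake is the decision to run a full trial. If the between-group result is inconclusive, as is likely at this sample size, a small p value for change in the immediate-access arm would be available, under an efficacy label, to meet the progression criterion.

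**Working it through.** The plan gives no figure for expected PHQ-9 change, so there is none to reproduce. The check asks how often a within-arm test would show improvement with no treatment effect, and how that compares with the power of the randomised contrast.

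**Inputs from the Protocol article.** Entry at PHQ-9 of 10 or more (Inclusion criteria); up to 50 participants (Sample size) allocated 50:50 (Overview), so 25 per arm; at least 75% follow-up (Outcome measures), so 0.75 × 25 = 18.75, about 19 per arm; assumed effect d = 0.58 and significance level 0.05 (Sample size).

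**Assumptions, not in the article.** PHQ-9 among people who respond to recruitment, before the cut-off is applied: mean μ from 8 to 14, SD σ of 5 to 6, correlation ρ between baseline and 3 months of 0.5 to 0.7. Scores are treated as normal and cut at 9.5, with no treatment effect and, at first, no natural recovery.

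**Formulas.** Let a = (9.5 − μ)/σ and λ = φ(a)/(1 − Φ(a)).

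- Mean of those selected: μ + σλ
- Variance of those selected: V = σ²(1 + aλ − λ²)
- Expected fall: (1 − ρ)σλ
- SD of change: √[(1 − ρ)²V + σ²(1 − ρ²)]
- Noncentrality of the paired t test: fall × √n / SD of change
- Chance of significant improvement: probability that the noncentral t exceeds the two-sided 5% critical value in the improvement direction, which is 2.5% if there is no change

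**Upper end** (μ = 8, σ = 5, ρ = 0.5): a = 0.30, λ = 0.998, V = 7.58. Fall = 0.5 × 5 × 0.998 = 2.50. SD of change = √(0.25 × 7.58 + 25 × 0.75) = 4.54. Noncentrality at n = 25 = 2.50 × 5/4.54 = 2.75, giving 75%; at n = 19, 62%. The largest fall comes with σ = 6: 0.5 × 6 × 0.964 = 2.89.

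**Lower end** (μ = 14, σ = 5, ρ = 0.7): a = −0.90, λ = 0.326, V = 15.0. Fall = 0.3 × 5 × 0.326 = 0.49. SD of change = √(0.09 × 15.0 + 25 × 0.51) = 3.76. Noncentrality at n = 25 = 0.49 × 5/3.76 = 0.65, giving 9%; at n = 19, 8%.

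| Source mean | Fall from selection alone | Significant improvement, 25 per arm | 19 per arm |
|---|---|---|---|
| 8 | 1.5–2.9 | 47–75% | 37–62% |
| 10 | 1.1–2.2 | 30–49% | 23–39% |
| 12 | 0.8–1.7 | 16–30% | 13–23% |
| 14 | 0.5–1.2 | 9–17% | 8–13% |

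**Adding natural recovery.** A simulation with scores rounded and held to 0–27 (SD 5; source mean 8, 12 or 14; correlation 0.5 to 0.8) and an assumed 2-point recovery in both arms gave significant within-arm improvement in 82% to nearly 100% of trials at 25 per arm and 69–98% at 19 per arm. The between-group test of change rejected in 4.5–5.7% of trials in every scenario, with or without recovery, which is its nominal 5%.

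**Power of the randomised contrast.** The two-sample t test at d = 0.58, two-sided 0.05, has power of about 52% at 25 per arm and 41% at 19 per arm. As a check on the method, it gives 80% at the article's 48 per group. (The power of 0.58 printed in Sample size does not yield 48; that is a separate matter and nothing here depends on it.)

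**Significant in the immediate arm only.** With no effect and probability p of significance in each arm, this pattern has probability p(1 − p). It peaks at 0.5 × 0.5 = 25%; at p = 0.75 it is 19% and at p = 0.30 it is 21%.

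**The case against.** The best defence is that the valid comparison is already planned: the sentence that sets the within-group tests goes on to the between-group differences, and the Overview names the delayed-access arm as the control. That stands. A reader might infer that the plan discards its control arm or lacks a randomised comparison; it does neither.

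Nor does the article say that efficacy will be judged from one arm's fall, or by comparing significance across arms. A reader might infer that progression turns on within-group p values, but the progression sentence names no contrast. The fault is that the article leaves this open while labelling both analyses as efficacy.

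A reader might also take the within-arm rejection rates as inflated type I error. They are not: the mean really does fall, so rejecting no change is correct. The error would lie in crediting the fall to the intervention.

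The size depends heavily on the assumed source mean. Means of 8–10 put the average responder near or below the cut-off and give 30–75% at 25 per arm. Recruitment aims at people with clinical levels of symptoms, so higher means are at least as plausible, and there regression to the mean alone gives 9–30%. Significance is therefore not assured, though the direction of the expected change does not depend on these values.

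Finally, the primary aim is feasibility, mood is secondary and efficacy is one of several progression elements. That limits the weight of the point but does not remove it, because the tests are expressly specified rather than left to a later document.

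**Conclusion.** The point holds as one of analysis choice and labelling. The article specifies significance tests that cannot separate treatment from selection and time, places them under efficacy, and does not exclude them from the progression decision. Under SD 5–6, correlation 0.5–0.7 and source mean 8–14, an untreated arm is expected to fall by about 0.5–2.9 points through regression to the mean alone. It would test as significantly improved about 9–75% of the time at 25 per arm and 8–62% at 19 per arm, and more often with natural recovery. All of these values are assumptions.

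With between-group power of about 52% or 41% at the article's own effect size, a significant within-arm fall beside a non-significant randomised comparison is a realistic result. One might infer that the two arms would routinely disagree on significance by chance. Disagreement in either direction can reach 2 × 0.25 = 50% only at its maximum, and the misleading direction never exceeds 25%. The correction should be made, but the randomised analysis itself is not undermined.

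**What to change.** In the Statistical analysis section:

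1. Remove the significance tests of within-group change from the efficacy analysis. Report each arm's baseline and 3-month means and its change, with SDs, as description only.
2. State that every efficacy statement rests on the already planned randomised between-group difference at 3 months, reported with its confidence interval.
3. State in the progression sentence that evidence of possible efficacy means that between-group estimate and interval, and not change within an arm.

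The cost is a change of text. Data collection, sample size and conduct are unaffected, and the within-arm means and SDs remain available for planning the full trial.

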## Discussion

### Importance of the project

Depression is the main contributor to the global burden of disease [1] and has a significant impact on sufferers’ lives. Despite the fact that there are various evidence-based interventions for depression [2], fewer than 50 % of those affected receive appropriate treatment for low mood [3]. Low-intensity interventions, such as online CBT courses can potentially bridge the gap between onset of depression and receiving appropriate treatment by increasing access to psychological therapies. The same LLTTF content has already been evaluated in its course (group classes) and book forms, showing significant improvements in depression, anxiety, quality of life and high levels of satisfaction [7, 9, Williams, McClay, Matthews, Haig, McConnachie, Morrison. A randomised controlled trial of a community based group guided self-help intervention for low mood and stress. Submitted]. The current pilot study will, however, represent the first RCT of the updated LLTTF online package and provide key information across a range of methodological uncertainties required for a full RCT of the LLTTF online package. These include community recruitment, uptake, delivery, adherence to the intervention and data collection, with results being used to determine the sample size needed for a substantive RCT.

### Benefits to participants

Participation within this research will allow adults who are experiencing mild to moderate symptoms of low mood or anxiety to use online CBT-based life skills and other educational modules aimed at addressing these issues. Previous research on other variants of the same course suggests that the LLTTF approach can be effective in aiding a variety of problems related to low mood and stress [7, 9, Williams, McClay, Matthews, Haig, McConnachie, Morrison. A randomised controlled trial of a community based group guided self-help intervention for low mood and stress. Submitted]. The satisfaction data will help us to gain a key insight into how online websites can be best delivered and supported in the community.

### Working with the voluntary sector

In this pilot study, the Scottish charity Action on Depression will deliver the support element of the intervention using a pre-established support protocol. Support workers from this depression charity are experienced in working with the proposed population and have experience of introducing and supporting self-help materials. They can also assist any individuals who may need further help during the study by signposting them to additional support if there is concern about a participant’s wellbeing. Action of Depression have an effective system for identifying and supporting individuals in the community and the involvement of this charity may aid in accessing hard-to-reach individuals, including young men and minority ethnic groups; as well as individuals who may prefer voluntary sector support rather than traditional treatment options offered via the NHS.

### Dissemination

We aim to disseminate the findings of this pilot study in an open-access journal and via conference presentations. The journal publication will present the study findings, with the data being used to inform a future RCT protocol and a grant application. A short summary of the findings of the study will be posted online via social media accounts. We will also disseminate findings via newsletters at www.livinglifetothefull.com, which receives around 30 million hits a year from members of the public and practitioners and our partners Action on Depression.

## Trial status

The website has been designed and tested. Recruitment is expected to begin in September 2015, with the collection of outcome data starting in December 2015.

## Abbreviations

CBT: cognitive behavioural therapy
LLTTF: ‘Living Life to the Full’
NICE: National Institute for Health and Care Excellence
RCT: randomized controlled trial
WHO: World Health Organization
